### Economic aspects

Globally, healthcare systems are grappling with escalating costs, heightening the imperative for efficiency in healthcare delivery. Consequently, it becomes crucial to optimize the utilization of public resources [18, 19]. Hence, a cost-effectiveness analysis will be conducted in the present study. To the best of our knowledge, no prior studies have explored the cost-effectiveness of Permissive Weight Bearing (PWB) versus Restricted Weight Bearing (RWB) in surgically treated patients with DIACFs.

### Evaluation of treatment

To date, one systematic review has compared the impact of time to post-operative weight bearing on functional and clinical outcomes in adults with DIACFs across 72 studies [10]. The sole Patient-Related Outcome Measure (PROM) examined in this review is the American Orthopaedic Foot and Ankle Society (AOFAS) score. According to these findings, EWB does not appear to lead to impaired functional outcomes when compared to more conservative weight bearing regimes [10]. However, the studies included in the comparison were categorized based on weight bearing, and no direct comparison of predetermined weight bearing regimes was conducted.

In recent years, the importance of healthcare efficiency has grown significantly. It is imperative to examine patient healthcare costs as well as costs to families and society for both treatment options. Surprisingly, these costs have not been explored in previous studies. This study will be the first prospective RCT to investigate these costs associated with both rehabilitation regimens.

## Methods: participants, interventions, and outcomes

### Study setting {9}

The PIONEER study will be structured as a prospective, randomized controlled, multicenter trial. It will be conducted in 11 medical institutions across the Netherlands, both urban and academic hospitals. All hospitals joined another study together and were asked to participate in the PIONEER study. Details regarding the locations of participating medical institutions are shown in Additional file 1. Both rehabilitation protocols will be available in all hospitals.

The study will adhere to the SPIRIT (Standard Protocol Items: Recommended for Interventional Trials) 2013 statement. Approval from the local medical ethics committee has been secured, with registration number: NL83269.068.23. Additionally, ‘the PIONEER study’ is registered in the ClinicalTrials.gov database under registration number: NCT05721378 as of 07/02/2023 and will be conducted in accordance with the principles outlined in the Declaration of Helsinki.

Over the course of a 1-year period, patients will be enrolled. Enrolment is commenced on July 1st, 2024. The participating institutions in the PIONEER study are specified in the Additional file 1.

### Eligibility criteria {10}

The study population comprises patients with surgically treated DIACFs, for whom weight bearing is prohibited for 8 to 10 weeks post-operatively in accordance with current guidelines. Specifically targeting individuals in the labor force, the inclusion criteria encompass patients aged between 18 and 67 years old, facilitating the estimation of reductions in healthcare and societal costs. Eligible patients must possess the capacity to comprehend and adhere to instructions. Written informed consent will be obtained from all participants before their inclusion in the study.

#### Inclusion criteria

Surgically treated (e.g., extended lateral, sinus tarsi, and percutaneous approach) trauma patients with isolated unilateral DIACFs, less than 6 weeks after the initial trauma, Sanders type II–IV [20]Isolated unilateral calcaneal fracturesAge between 18 and 67 years old (labor force)Being able to understand the questionnaires and measurement instructionsIndication for open/closed reduction and internal fixationWritten Informed Consent

#### Exclusion criteria

Acute or existing amputation (upper limb, lower limb, feet)Open calcaneal fractures (excluding medial wound without compromising surgical approach)Unable to comply to the PWB protocol due to pre-existing conditions of the arms and legs (e.g. unable to use crutches due to hemiparalysis)Severe non-fracture-related comorbidity of the lower extremityPre-existent immobility (loss of muscle function of one or both legs)Dependent in activities of daily living (e.g. due to dementia, Alzheimer, New York Heart Association class IV angina, heart failure, or oxygen-dependent chronic obstructive pulmonary disease)Rheumatoid arthritis of the lower extremitiesSevere psychiatric comorbidities that lead to the inability to comply with the treatment protocolPathologic fractures (metastasis, secondary osteoporosis)Peripheral neuropathy and/or diabetesAlcohol- or drug abuse preventing adequate follow-upPrimary indication for arthrodesis subtalar joint

### Who will take informed consent? {26a}

The physician, who holds clinical responsibility for the patient, will bring the study to the patient's attention. If necessary, the physician will provide the patient with an information folder about the study and contact the investigator to discuss inclusion criteria. Due to the inherent dependency relationship between the doctor and patient, a Local Investigator (LI) will be assigned in each hospital. The LI will explain the study to the patients, providing them with a detailed patient information letter and verbal explanation, and then seek their willingness declaration. This interaction will only occur after the patient has given permission to be approached by the investigator.

Patients will be given 1 week postoperatively to decide whether to participate. The consideration period will commence once the patients receive the patient information folder and the oral explanation. Signing the informed consent letter will only occur after patients have had the opportunity to ask any additional questions, ensuring their understanding of participation. If patients agree to participate, the informed consent letter will be completed in the presence of the investigator and stored at the investigation site.

### Additional consent provisions for collection and use of participant data and biological specimens {26b}

Not applicable; no biological specimens will be collected.

## Interventions

### Explanation for the choice of comparators {6b}

The absence of prospective studies on weight bearing protocols prevents the favoring of one rehabilitation regimen (PWB or RWB) over the other in the treatment of surgically managed trauma patients with DIACFs. Consequently, there is a clear need for a large-scale prospective, high-quality RCT to evaluate whether the PWB protocol yields improved functional outcomes, radiographical parameters, enhanced quality of life, and reduced costs. Such a trial should also examine cost-effectiveness and complications, as cost considerations could be pivotal in decision-making, particularly when both rehabilitation regimens yield comparable PROMs.

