## Abstract

**Background:**

Following successful treatment, displaced intra-articular calcaneal fractures (DIACFs) necessitate an extensive rehabilitation regimen, significantly influencing functional and socio-economic outcomes. Apart from surgical intervention, the implementation of a comprehensive rehabilitation protocol is crucial to optimize foot stability and functional recovery. The objective of this study is to ascertain the optimal rehabilitation protocol for patients with surgically treated DIACFs, either permissive weight bearing (PWB) or Restricted Weight Bearing, focusing on functional outcomes, health-related quality of life (HRQoL), radiographic parameters, cost-effectiveness, and incidence of complications.

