### Objectives {7}

The purpose of ‘the PIONEER study’ is to conduct a randomized controlled trial in surgically treated patients with DIACFs who undergo rehabilitation with either PWB or Restricted Weight Bearing (RWB). The primary aim of the study is to explore functional outcomes for surgically treated patients with DIACFs and will be allocated to one of the two distinct rehabilitation protocols (PWB or RWB) over a 6-month period. Secondary objectives include comparing disparities in additional functional outcomes and health-related quality of life (HRQoL). Additionally, variances in radiographical parameters (Böhlers angle and posterior facet joint alignment), cost-effectiveness, and complication rates will be assessed and compared.

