### Trial design {8}

The PIONEER study will be a prospective multicenter RCT conducted in the Netherlands, with parallel groups, allocation ratio 1:1. The primary outcome measure will be evaluated based on the principles of non-inferiority. Secondary outcomes on superiority.

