#### Primary study parameter

For the primary research question, the AOFAS Score at 6 months, a continuous outcome, will be utilized. The relative effectiveness of PWB compared to RWB on the AOFAS score will be analyzed using a linear regression model. The model will be adjusted for the type of surgery and hospital. The objective is to assess the non-inferiority of PWB compared to RWB, with a non-inferiority margin set at 5 points. To evaluate non-inferiority, a two-sided hypothesis test will be conducted to determine whether the lower limit of the confidence interval for the estimated treatment effect exceeds the predefined non-inferiority margin. The corresponding p-value for non-inferiority will be calculated using the input from the estimated model. The assumptions for the linear regression model will be evaluated, including linearity, independence of errors, homoscedasticity, and normality of residuals.

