## Discussion

The current paper outlines the protocol for a multicenter randomized controlled trial to be conducted in 11 hospitals across the Netherlands. It provides comprehensive details on the study’s objectives, methodology, including patient flow, randomization procedures, recruitment strategies, rehabilitation protocols, and data analysis methods. Additionally, it offers guidance for presenting and publishing the results. Notably, this study will be the first to establish an optimal rehabilitation regimen for patients with DIACFs, and it possesses several strengths. Firstly, it adopts a randomized controlled trial design, widely regarded as the gold standard in clinical research. The involvement of multiple Dutch hospitals enhances the generalizability of the findings. Moreover, this design minimizes potential biases inherent in observational studies, facilitating a more accurate assessment of intervention effectiveness.

However, several limitations should be acknowledged. Firstly, the inevitable heterogeneity in surgical treatment across participating centers may impact protocol consistency and consequently, outcomes. Standardized protocols and staff training will address this concern. Secondly, compliance bias may arise as patients may not strictly adhere to allocated weight bearing regimes. Again, standardized protocols and staff training will mitigate this bias. Thirdly, patient blinding is unfeasible for rehabilitation, potentially compromising methodological rigor and introducing bias into results. However, blinding will be implemented for radiological evaluations. Additionally, the 1-year follow-up period limits assessment of longer-term outcomes, although the greatest effect of early weight bearing is typically observed within the first 3 to 6 months post-surgery.

In conclusion, existing retrospective literature provides inadequate methodological data to determine the superiority of one rehabilitation protocol over another. The PIONEER study will offer evidence on whether to favor one weight bearing protocol over another and will ascertain the safety and efficacy of these protocols for patients with DIACFs.

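### The plan asks whether PWB improves function but pre-specifies only non-inferiority on the AOFAS; a superiority step in fixed sequence would cost nothing

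*Protocol article*

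**What the plan says.** The protocol article describes its question in several ways.

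- **Abstract, Background:** "The objective of this study is to ascertain the optimal rehabilitation protocol for patients with surgically treated DIACFs", judged on function, quality of life, radiographic parameters, cost-effectiveness and complications together.
- **Objectives {7}:** a neutral aim, "The primary aim of the study is to explore functional outcomes for surgically treated patients with DIACFs".
- **Explanation for the choice of comparators {6b}:** a trial is needed "to evaluate whether the PWB protocol yields improved functional outcomes, radiographical parameters, enhanced quality of life, and reduced costs". The next sentence adds that costs could decide the matter if the two regimens give comparable patient-reported outcomes.
- **Discussion:** the study "will offer evidence on whether to favor one weight bearing protocol over another".

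The formal framework is narrower. Trial design {8} says: "The primary outcome measure will be evaluated based on the principles of non-inferiority. Secondary outcomes on superiority". The section Primary study parameter says: "The objective is to assess the non-inferiority of PWB compared to RWB, with a non-inferiority margin set at 5 points". The analysis there is a linear regression of the 6-month AOFAS, adjusted for type of surgery and hospital, with a two-sided test that compares the lower confidence limit with the margin. No section mentions a superiority test on the AOFAS, and none rules one out.

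**The concern.** Meeting a 5-point non-inferiority margin shows that PWB is not worse than RWB by more than 5 points. It does not show that PWB is better. The rationale speaks of improved function and the Discussion of favoring one protocol, but the only pre-specified test on the primary endpoint addresses neither.

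Two results show what is at stake.

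- **A small negative estimate that passes the margin.** The loose wording would allow this to be reported as settling which regimen is preferable on function, although it shows only that PWB is not much worse.
- **A clearly positive estimate.** This would be evidence of benefit. But Trial design {8} expressly gives superiority to the secondary outcomes, so a critic could call a superiority claim on the AOFAS post hoc.

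**Working it through.** **Inputs.** From Sample size {14}: SD 8.5, alpha 5%, power 80%, true difference 0, 46 per group, 92 in total, 115 recruited with 20% dropout. From Primary study parameter: margin 5 points, two-sided test, time point 6 months.

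**Step 1: reproduce the plan's sample size.** For non-inferiority of two means with true difference 0:

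n per arm = 2 × (z_alpha + z_beta)² × SD² / margin²

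- One-sided 2.5%: 2 × (1.960 + 0.842)² × 8.5² / 5² = 45.4, rounded up to 46. That gives 92 in total, and 92 / 0.80 = 115. This matches the plan.
- One-sided 5%: 36 per arm, which does not match.

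The 5% is therefore two-sided, and the interval that goes with the sample size is a two-sided 95% interval.

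**Step 2: what that interval can show.**

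- SE = 8.5 × √(2/46) = 1.77.
- Half-width = 1.96 × 1.77 = 3.47.
- Non-inferiority (lower limit above −5) needs an estimate above −5 + 3.47 = −1.53.
- Superiority (lower limit above 0) needs an estimate above +3.47.

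An estimate of −1 has an interval of about −4.5 to +2.5, which is non-inferior and nothing more. An estimate of +5 has an interval of about +1.5 to +8.5, which is non-inferior and also above zero.

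**Step 3: power for superiority at the planned size.** Power = 1 − Φ(1.96 − d/SE), with 46 per arm:

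| True PWB benefit d (points) | Power |
|---|---|
| 2 | 20% |
| 3 | 39.5% |
| 4 | 62% |
| 5 | 80.5% |
| 6 | 92% |

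The superiority sample size for a 5-point benefit is also 46 per arm. The formula in Step 1 applies unchanged, with the benefit in place of the margin.

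**Step 4: does the second step cost alpha?** A lower limit above 0 is necessarily above −5, so the two claims are nested. In a simulation of 400,000 estimates with SE 1.77, reading both claims from one 95% interval gave a false non-inferiority rate of 2.5% at a true difference of −5. The false superiority rate was 2.5% at a true difference of 0. Neither error rate is inflated.

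**The case against.** The strongest reply is that nothing is wrong with the design.

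- **The wording is broader than function.** The comparator section is background, and its next sentence foresees comparable patient-reported outcomes with costs deciding, which is non-inferiority reasoning. The abstract's objective spans five kinds of outcome. The abstract's Methods, Trial design {8} and the primary analysis all agree on non-inferiority. This stands: non-inferiority is a legitimate primary aim, and no reader is misled about the primary test.
- **The interval already shows benefit.** A reader might infer that the trial could not conclude a clear PWB benefit on the AOFAS, or cannot answer its question. The documents do not support that. The planned two-sided interval would show a benefit if its lower limit exceeded 0, and endpoint, time point and model are already fixed. What is absent is the pre-stated claim.
- **Function is tested for superiority elsewhere.** The Maryland Foot Score is a functional score among the secondary outcomes, which Trial design {8} places on superiority. This stands only in part: it is not the primary endpoint, and Secondary study parameters describes its analysis as similar to the primary one, so its framework is less clear than it could be.
- **The step may be in an analysis plan or full protocol not shown.** That is possible, and a missing sequence would not by itself be a finding. But Trial design {8} states the split expressly, so an analysis plan with this step would be adding to the published framework. The broader wording of the rationale and Discussion is in this article in any case.

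**Conclusion.** The point holds as a free improvement, not as an error in the design. The rationale and Discussion ask whether PWB improves function and which protocol to favor. The published framework tests the primary AOFAS for non-inferiority only and reserves superiority for secondary outcomes. A benefit on the AOFAS could be seen in the planned interval, but no route to claim it is pre-specified.

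The chance of using such a route depends on the true effect: about 80% at 5 points, 62% at 4 and 39.5% at 3. These figures assume 46 evaluable patients per arm, SD 8.5 and a simple two-group comparison. Adjustment for surgery type and hospital would change the SE somewhat. Sample size, alpha and the non-inferiority conclusion are unaffected.

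**What to change.** 1. **Trial design {8} and Primary study parameter:** add that, if non-inferiority is established, superiority of PWB on the 6-month AOFAS is tested next in fixed sequence. It uses the same regression model and the same two-sided 95% confidence interval (lower limit above 0), in the intention-to-treat set. The set should be named because the section on statistical methods {20a} lists both intention-to-treat and per-protocol analyses without saying which governs.
2. **Discussion:** state that, if only non-inferiority is shown, the conclusion on the AOFAS is that PWB is not worse by more than 5 points. Any preference for PWB then rests on the secondary outcomes and costs.

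The cost is a few sentences, ideally written before any outcome data by arm are seen. No alpha, patients or extra data are needed.

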### Intervention description {11a}

#### Permissive weight bearing

The PWB protocol represents a relatively new approach to early weight bearing, enabling earlier postoperative weight bearing. Progression of weight bearing is determined by the patient’s subjective experience, such as pain levels and weight bearing tolerance, along with the clinical expertise of the treating physician and physiotherapist, in line with the PROMETHEUS protocol [12]. The rehabilitation regimen commences with 2 weeks of immobilization to facilitate wound healing. Subsequently, patients are allowed to bear as much weight as tolerated, guided by their pain levels and comfort [12].

#### Restrictive weight bearing

The RWB protocol adheres of 8 to 12 weeks of postoperative weight bearing restriction, in the range of 0–10%, so-called *touching load*, as outlined in the current AO Guidelines [16]. Following this initial phase, which entails restricted weight bearing, a gradual increase in weight bearing is implemented. This entails a weekly increment of 25% over the course of 4 weeks. During each patient-physician encounter, the weight bearing advice provided to the patient is meticulously recorded. This includes whether the recommendation is for unloaded, partial weight bearing with clarification, or full weight bearing. Furthermore, any additional advice imparted to the patient is also documented.

### Criteria for discontinuing or modifying allocated interventions {11b}

In accordance with Sect. 10, subsection 4 of the WMO, the sponsor will suspend the study if there is sufficient reason to assume that continuing the study would compromise the health or safety of the subjects. The sponsor will promptly notify the accredited Medical Ethical Board of any temporary suspension, providing the reasons for such action without undue delay. The study will remain suspended until a further (positive) review from the accredited Medical Ethical Board is obtained. Throughout this process, the Coordinating Investigator (CI) will ensure continuous communication with the enrolled subjects.

Besides, the LI or CI reserves the right to withdraw a participant from the study due to urgent medical reasons. Participants retain the autonomy to withdraw from the study at any point for any reason, without facing any repercussions. Data collected up until the time of withdrawal will be utilized for study purposes.

### Strategies to improve adherence to interventions {11c}

This is not applicable to our study, as strategies to improve adherence to intervention protocols and procedures for monitoring adherence are not required.

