## Statistical methods

### Statistical methods for primary and secondary outcomes {20a}

Baseline patient characteristics will be presented according to the by aftertreatment regime. Continuous variables will be summarized using either mean and standard deviation or as median and interquartile range. Categorical variables will be summarized as count and percentages.

All analyses of the primary and secondary study parameters will be conducted following both the intention-to-treat principle and the per-protocol principle. Statistical significance will be determined using a *p*-value of ≤ 0.05. All analyses will be carried out using “R” or IBM SPSS version 28 or later.

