### Methods in analysis to handle protocol non-adherence and any statistical methods to handle missing data {20c}

Missing data will be addressed through stochastic regression imputation. In addressing protocol non-adherence, the analysis will be conducted on an intention-to-treat (ITT) basis, including all participants as originally assigned regardless of their adherence to the study protocol. For handling missing data, multiple imputation techniques will be employed to ensure the robustness and validity of the statistical analyses.

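### A per-protocol analysis of the non-inferiority primary outcome is promised, but monitoring of adherence is declared unnecessary and only the advice given, not the loading practised, is recorded

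*Protocol article*

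**What the plan says.** All references are to the Protocol article.

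- **Trial design {8}:** "The primary outcome measure will be evaluated based on the principles of non-inferiority".
- **Primary study parameter:** for the primary question, "the AOFAS Score at 6 months, a continuous outcome, will be utilized", "with a non-inferiority margin set at 5 points". The lower confidence limit is compared with the margin.
- **Statistical methods {20a}:** all primary and secondary analyses are to be "conducted following both the intention-to-treat principle and the per-protocol principle".
- **Strategies to improve adherence {11c}:** the item is marked not applicable because "strategies to improve adherence to intervention protocols and procedures for monitoring adherence are not required".
- **Restrictive weight bearing, under {11a}:** at each visit "the weight bearing advice provided to the patient is meticulously recorded". This is what the patient was told. The outcomes section {12} and the data-collection section {18a} describe no measure of the patient's own loading.
- **Non-adherence and missing data {20c}:** to address non-adherence, "the analysis will be conducted on an intention-to-treat (ITT) basis".
- **Discussion:** "compliance bias may arise as patients may not strictly adhere to allocated weight bearing regimes", to be mitigated by standardized protocols and staff training.

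Three other places bear on adherence. Section {5d} has the study team review adherence to the protocol at roughly quarterly meetings. Section {23} provides independent audits after every five patients per center. Section {25} has protocol deviations documented on a breach report form.

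**The concern.** The two arms differ only in how much the patient loads the foot and when. The allocation is open, and much of the loading happens at home between visits. In this setting a per-protocol analysis is informative only if the trial knows what patients did. A statistical analysis plan can define a per-protocol set only from data that were collected, so it cannot make good a protocol decision not to monitor adherence. If the set were built on the advice log alone, an RWB patient who was told not to load but walked on the foot at week 4 would count as adherent.

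What is at stake is the primary conclusion. In a superiority trial, loss of contrast between arms usually works against the claim. In a non-inferiority trial it can work for it: if PWB is truly worse, early loading in the RWB arm brings that arm's result towards the PWB result, shrinks the deficit seen under ITT, and makes it easier to clear the margin. The per-protocol result is the usual check on this.

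**Working it through.** **1. Inputs.** Margin 5 points (Primary study parameter). From Sample size {14}: SD 8.5, true difference 0, alpha 5%, power 80%, 46 per group, 92 evaluable, 115 recruited with 20% dropout. The confidence-interval test is two-sided, which equals one-sided 2.5% at the lower limit.

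**2. The plan's own figure.** n per group = 2 × (1.960 + 0.842)² × 8.5² / 5² = 45.4, rounded up to 46. Total 92, and 92 / (1 − 0.20) = 115. All three figures reproduce. (One-sided 5% would give 36 per group, so the plan did use 2.5% one-sided.) The sample size is not in question.

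**3. Effect of lost contrast on the ITT test.** The documents give no non-adherence rate, so d below is an assumption shown as a range. It is the share of the full-adherence difference between arms that is lost. It equals the share of RWB patients who behave fully like PWB patients if only that arm departs from its regime. Partial early loading would cost less than a full crossover.

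- SE = 8.5 × √(2/46) = 1.772
- True difference under full adherence = −5 (PWB worse by exactly the margin)
- ITT difference = −5 × (1 − d)
- P(non-inferiority declared) = Φ((5 + ITT difference)/SE − 1.96)

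| d | ITT difference | (5 + difference)/SE − 1.96 | False non-inferiority |
|---|---|---|---|
| 0 | −5.0 | −1.96 | 2.5% |
| 10% | −4.5 | −1.68 | 4.7% |
| 20% | −4.0 | −1.40 | 8.1% |
| 30% | −3.5 | −1.11 | 13.3% |
| 40% | −3.0 | −0.83 | 20.3% |

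At d = 20% the error is more than three times the nominal 2.5%. If the true difference is zero, dilution does not move the estimate.

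**4. Cost in the per-protocol set.** Suppose a share of the 46 per arm is excluded and the true difference is 0. Power = Φ(5/SE − 1.96) with the reduced n.

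| Excluded | n per arm | SE | Power |
|---|---|---|---|
| 0 | 46 | 1.772 | 80.5% |
| 10% | 41.4 | 1.868 | 76.3% |
| 20% | 36.8 | 1.982 | 71.3% |
| 30% | 32.2 | 2.118 | 65.6% |

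**5. The texts side by side.** {20a} needs adherence data and {11c} says they need not be gathered. {5d} and {25} assume that some adherence and deviation information exists. The Discussion expects non-adherence and answers it with training and standardization, although {11c} says that adherence strategies are not required. These statements do not fit together.

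**The case against.** The strongest reply is that the protocol is not silent on adherence. Deviations go on breach forms, the team reviews adherence about quarterly, sites are audited, and advice is logged at each visit. A per-protocol set could be assembled from these. That stands in part: a crude set is possible, so a reader who infers that no per-protocol analysis could be done, or that the conclusion would necessarily rest on ITT alone, goes beyond the text. But these are trial-conduct measures. None describes recording each patient's loading, and early loading at home that nobody asks about is unlikely to reach a breach form.

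Four further readings are tempting and not supported:

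- *That {20c} withdraws the per-protocol analysis.* It can be read as explaining how ITT treats non-adherers, alongside {20a}.
- *That the lack of a rule on which set decides is an error.* Such a rule is commonly left to the analysis plan, which is not shown.
- *That PWB patients who hold back are non-adherent.* Section {11a} defines PWB by what the patient tolerates, so light loading because of pain is within that regime. The dilution that matters would come mainly from the RWB arm.
- *That both sets must clear the margin.* This is a design choice with a real price in power, and excluding patients after randomization brings selection bias of its own.

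It is also fair to say that the error rates above are hypothetical. They depend on an unstated non-adherence rate, on linear dilution, and on PWB being truly worse. The last is, however, the case that the test exists to guard against.

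**Conclusion.** The point holds in limited form. The protocol commits to a per-protocol analysis of a non-inferiority outcome while declaring that adherence need not be monitored, and the weight-bearing item it records is the advice given rather than the behaviour. The resulting per-protocol set would be crude and a weak check on the ITT result. Sections {11c}, {5d}, {25} and the Discussion need to be reconciled.

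The size cannot be fixed from the documents. Under the stated assumptions (true deficit of 5 points, SD 8.5, 46 per arm, linear dilution), losing 10% to 40% of the contrast raises the false non-inferiority rate from 2.5% to between 4.7% and 20.3%. This is an illustration of the risk, not a prediction for this trial.

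**What to change.** 1. Replace the statement in {11c} with a plan to record adherence. In the questionnaires already sent at 2, 6 and 12 weeks, ask what weight bearing the patient actually practises (none, touch, partial, full) and the dates of first partial and first full loading. RWB as described can reach full loading at 12 to 16 weeks (8 to 12 weeks plus a 4-week build-up), so some of those dates may have to be completed at the 6-month questionnaire.
2. Define the per-protocol set from these answers and the recorded deviations before database lock.
3. Report the per-protocol estimate and confidence interval beside the ITT result for the primary non-inferiority comparison.
4. Align {5d}, {25} and the Discussion with the revised {11c}.

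Whether both sets must clear the margin is for the sponsor to decide, with the power figures above in view.

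The cost is one or two extra items in existing questionnaires plus wording. The answers are unblinded self-report, and the per-protocol set will be less precise than the ITT set. The change is best made early, because loading that is not asked about at the time cannot be reliably reconstructed later.
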